8.1 Response Rate

All eligible patients will be included in the response rate calculation. The subgroups that designated a response category (CR, PR, ED, and disease progression - PD; see definitions below) are all patients who received at least one dose of study medications.

Radiological response

Response and progression will be assessed in this study using the new international criteria proposed by the RECIST v1.1 committee (Response Evaluation Criteria for solid tumors). Changes only in the larger diameter (one-dimensional measurement) of tumor lesions are used in the RECIST v1.1 criteria (Appendix

2).

9. Toxicity Assessment

Adverse Events (EA) will be classified using the Common Terminology Criteria of the American Cancer Institute for Adverse Events Version 4.0 (NCI - CTC AE) (73). All patients will be evaluated for study drug toxicity from the time of their first treatment dose until at least 28 days after the last dose.

10. Statistical Considerations

10.1 Statistical design and sample size

This is a prospective, unicenter, single-stage, phase 2, two-stage study to investigate the efficacy and safety of the combination of irinotecan and metformin in patients with metastatic colorectal cancer, to be a promising regimen for further extension to a phase 3 trial. The primary end point is the disease control rate at week 12 of treatment.

Simon's optimized two-stage procedure will be used for the sample calculation. (76) Considering a DCR of 13,2% on week 12 with placebo in third line, we believe that it would be clinically significant to increase this DCR to 26,7% Considering an alpha error of 10% and a beta error of 20%, we planned to enroll 41 patients. This study would be considered positive if at least 9 patients had disease control on week 12 (16). We believe this increase in the rate of disease control is feasible in light of the preliminary analysis of preclinical data presented by our group and other ongoing clinical protocol in our services that assesses metformin combined with chemotherapy (PPSUS 2011 Project - FAPESP Support - http://clinicaltrials.gov/show/NCT01333852 ).

Secondary objectives will be safety and tolerability, quality of life, SLP, and SG. Whole blood and fractions will be collected and deposited in our biobank to enable future evaluation of host and tumor serum response and prognostic markers. (77) Efficacy outcomes will be analyzed according to intention-to-treat (ITT).Safety outcomes will be assessed across the population exposed to study medications.

11. Recruitment and Study Duration

The estimated recruitment for this study is 41 patients. The study recruitment period will be estimated at 22 months, and all patients will remain on treatment and follow-up until disease progression. The total period of the study will last two years and may be extended as the recruitment rate is lower than expected, after discussion with internal monitoring bodies, Barretos Research Ethics Committee.

There will be continuous monitoring of the results and progress of the study by the Research Ethics Committee, as routine, in order to ensure the safety of the research subjects. If necessary, the study may be discontinued early, either because of futility, insecurity or early attainment of its positive outcomes at the end of the first phase of the study. Those patients who progress or are excluded from the study will be monitored for survival assessment.

The study period for each patient is defined as the day of patient inclusion until:

• The day when an event (disease progression as defined by RECIST, or death) is observed in this patient;

• The day when the patient discontinues treatment due to an unacceptable adverse event, withdrawal of consent or discontinuation of the study, or for any other reason than 21 days.

All those who discontinue treatment for any reason will be followed for survival assessment.

Patients who demonstrate disease progression during the study or who discontinue the study drug for any reason other than disease progression and withdrawal of consent (ie adverse event, administrative reasons, etc.) will have their survival accompanied. The designated investigator will contact the patient monthly for survival information and additional antineoplastic therapies.

12. Statistical Analysis

The primary end point is disease control rate at week 12, which is the sum of complete response, partial response, and stable disease in this assessment. Dichotomous efficacy outcomes, as well as patient baseline characteristics and adverse events, will be analyzed by Fisher's exact test and the Χ² test. For survival analyzes, progression is defined as radiological progression (RECIST 1.1) (72) or death from any cause. Progression free survival (SLP) and overall survival (SG) will be estimated by the Kaplan-Meier method. Other results will be reported using descriptive statistics. SPSS software version 14.0 or later as available (SPSS Inc., Chicago-IL, United States) will be used for statistical analysis of the results.

13.  Procedures and Data Collection

Data will be collected in the case report form ([CRF] supplement 1) and recorded in a specific study database at the Research Support Center of the Barretos Cancer Hospital. The original completed CRF will be sent to the principal investigator.

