16.1 Patient Protection

The responsible investigator will ensure that this study is conducted in accordance with the Declaration of Helsinki (amendments from Tokyo, Venice, Hong Kong, Somerset West and Edinburgh) or with the laws and regulations of the country providing the highest patient protection.

The protocol has been written and the study will be conducted in accordance with the Tripartite Guidelines of the International Conference on Harmonization for Good Clinical Practice (http://www.ifpma.org/pdfifpma/e6.pdf).

The protocol has already been approved by the HCB Research Ethics Committee, which considered it unnecessary to submit for evaluation by the National Research Ethics Committee (CONEP). There will be continuous monitoring of safety and efficacy results by the Research Ethics Committee (CEP-HCB), as routine, in order to ensure the safety of the research subjects. If necessary, the study may be discontinued early either due to futility, lack of security or early achievement of its positive outcomes.

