16.3 Informed Consent

All patients will be informed of the study's intentions, possible adverse events, procedures and possible risks to which they will be exposed. They will be informed of the strict confidentiality of their data and that their medical records will only be accessible to members assigned to conduct and monitor the study, such as researchers and members of the Barretos Research Ethics Committee.

It will be emphasized that participation is voluntary and that the patient has the right to refuse further participation in the protocol at any time. This will not impair subsequent patient care. Documented Informed Consent (Supplement 2) must be obtained from all patients included in this study before they are enrolled in the study. This will be done in accordance with national and international regulatory requirements.

17. Administrative Responsibilities

It is the responsibility to store the records and medical records related to the protocol. The responsible team will comply with current legislation and international standards. These forms will be in physical form (case report form [CRF]) and will be kept under study centers for a minimum of five years.

18. Schedule

The total study time is 22 months and the table below describes the steps to be taken. The date D0 implies the day of submission to our zip code. We believe it is possible to submit in July 2013. We also believe it is feasible to include 2 patients per month. The number of eligible patients is higher, however, we seek to be conservative in order not to overload the outpatient routine of the oncology, radiology or NAP department. It is important to remember that there is a possibility that the study may be interrupted by futility until June 28, 2014, or earlier, if this decision is taken jointly between the researcher and the HCB bodies involved (CEP and NAP).

Table 4: Proposed Study schedule.

| Phase | Duration | Start* | Finish * |
| --- | --- | --- | --- |
| Inclusion and treatment of  17 patients in the 1st stage | 240 days | 01.10.2013 | May 31, 2014 |
| Time to first stage patient evaluation | 30 days | 06/01/2014 | June 30, 2014 |
| Inclusion and treatment of  24 patients of the 2nd stage | 300 days | 01.07.2014 | May 31, 2015 |
| Tumor assessment of 2nd stage patients | 30 days | June 1, 2015 | June 30, 2015 |
| Statistical analysis | 30 days | 01.07.2015 | Jul 31, 2015 |
| Article Writing | 30 days | Aug 01, 2015 | Aug 31, 2015 |

*: Estimated start and end.

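### Sections 11 and 16.1 permit an early stop for success with no boundary, so the plan does not control its 10% alpha; Table 4 also dates the stage-1 look before about a quarter of the 17 patients would have a week-12 result

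*Protocol*

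**What the plan says.** **Design (Protocol, Section 10.1).** "Simon's optimized two-stage procedure will be used for the sample calculation". The null rate is given as "Considering a DCR of 13,2% on week 12 with placebo in third line", and the target is that it would be "clinically significant to increase this DCR to 26,7" percent. The error rates and size are "alpha error of 10% and a beta error of 20%, we planned to enroll 41 patients". The only decision rule is that 9 or more disease controls at week 12 make the study positive. No stage-1 cut appears, for futility or for success.

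**Early stopping (Sections 11 and 16.1).** Section 11 (Recruitment and Study Duration) allows the study to be discontinued "either because of futility, insecurity or early attainment of its positive outcomes at the end of the first phase of the study". Section 16.1 (Patient Protection) provides for "continuous monitoring of safety and efficacy results by the Research Ethics Committee" and again allows a stop once positive outcomes are achieved, this time without tying it to the end of stage 1.

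**Timing (Section 18, Schedule, and Table 4).** Stage 1 includes and treats 17 patients from 1 October 2013 to 31 May 2014. The row "Time to first stage patient evaluation" runs from 1 to 30 June 2014, and the 24 stage-2 patients start on 1 July 2014. On accrual the text says "We also believe it is feasible to include 2 patients per month". It also mentions a possible interruption for futility by 28 June 2014. All dates are footnoted as estimates.

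**The concern.** A Simon two-stage design makes one interim decision, whether to stop for futility. Its alpha is calculated on the basis that success can be claimed only at the end. A permission to claim success at stage 1 adds a second route to a false positive that the stated 10% does not include. With no boundary, the people looking at the data would choose the size of that addition. A result of 4 of 17 is 23.5%, above the final threshold of 9/41 = 22.0%, so it could pass for a positive outcome.

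The timing matters for the other interim decision. The endpoint needs 84 days and the evaluation row allows 30. If the futility decision were taken with results outstanding and those patients treated as not controlled, it would lean towards stopping an active regimen. No sentence says the decision waits for all 17.

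**Working it through.** **Inputs.** p0 = 0.132, p1 = 0.267, N = 41, success if 9 or more (Section 10.1); n1 = 17, n2 = 24, the dates and 2 patients per month (Section 18, Table 4); endpoint at 12 weeks = 84 days. The sidedness of alpha is not stated and is taken as one-sided, as in a Simon design. The futility cut r1 (stop if r1 or fewer of 17) is not stated; I use none, 1 and 2 as assumptions.

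**Step 1: the plan's own figure.** For a single look at 41, P(X ≥ 9) is 0.083 under p0 (alpha) and 0.804 under p1 (power). The stated 10% and 80% are met.

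**Step 2: add a success cut s at stage 1.** With X ~ Bin(17, p) and Y ~ Bin(24, p),

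P(positive) = P(X ≥ s) + Σ over x from r1+1 to s−1 of P(X = x) · P(Y ≥ 9 − x).

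Example under p0 with s = 4: P(X ≥ 4) = 0.178. The second term is 0.030 with no futility stop and 0.019 with r1 = 2, giving 0.208 and 0.197.

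| Success cut at 17 | Alpha (r1 = 2 to no futility stop) | Power (same range) |
|---|---|---|
| none | 0.072-0.083 | 0.751-0.804 |
| 4 | 0.197-0.208 | 0.813-0.866 |
| 5 | 0.105-0.117 | 0.772-0.825 |
| 6 | 0.078-0.089 | 0.755-0.809 |
| 7 | 0.073-0.084 | 0.751-0.805 |
| 9 | 0.072-0.083 | 0.751-0.804 |

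Alpha exceeds 10% for a cut of 5 or fewer and stays below it for 6 or more. At 9 nothing changes, because the final rule has already been met. For any fixed futility cut, power rises or is unchanged.

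**Step 3: timing.**
- A week-12 result by 30 June 2014 needs entry by 30 June − 84 days = 7 April 2014.
- At 2 per month with the first entry on 1 October, the 17th enters about 1 June and reaches week 12 about 24 August; 13 of 17 have a result by 30 June.
- With the first entry half a month later, the 17th enters about 16 June and reaches week 12 about 8 September; 12 of 17 have a result.
- With even accrual to 31 May, the last patient reaches week 12 on 23 August; 13 of 17 have a result.
- Entering all 17 in the 188 days to 7 April needs about 2.6 to 2.8 per month (16 or 17 accrual intervals over 6.2 months).

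**Step 4: worst case for power.** Suppose the futility decision uses m patients with results and counts the rest as not controlled, while their true results still count at the end if the trial continues. Then

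power = Σ over x from r1+1 to m of P(X_m = x) · P(Y_(41−m) ≥ 9 − x), at p1.

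| Assumed r1 | All 17 read | 13 read | 12 read |
|---|---|---|---|
| 1 | 0.794 | 0.758 | 0.740 |
| 2 | 0.751 | 0.639 | 0.595 |

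**The case against.** A reader might infer that neither the 10% alpha nor the power holds. The documents do not support that. No stage-1 success cut is given, so alpha is undetermined rather than shown to be exceeded. The 9-of-41 rule leaves some room below 10%, and any success cut of 6 or more of 17 keeps alpha under it. The 20-21% figure needs a stop at 4 of 17, a cut found nowhere in the protocol. The success stop also does not reduce power.

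A reader might also infer that the stage-1 look cannot be complete on the scheduled dates. That too goes beyond the text. The dates are estimates, the stage-1 row covers treatment as well as inclusion, and Section 18 calls 2 per month conservative, with more patients eligible. Accrual finished by 7 April would make the look complete. Nor does the protocol say that pending patients count as failures or that the decision is taken without them.

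Finally, Section 11 describes monitoring for the safety of participants; only Section 16.1 mentions efficacy results. Both read as routine ethics-committee oversight rather than a plan for repeated testing.

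These limits stand. Two facts survive them: the permission to stop for success is written twice with no boundary, and the protocol's own rate, window and endpoint do not fit together. Table 4 leaves the same 30-day gap after stage 2, so the gap is not confined to one row.

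**Conclusion.** The point holds in a limited form. The plan permits an early success claim that its design and its single success rule do not provide for, so it does not control the 10% alpha. For one stage-1 look, the false-positive rate would be about 0.20-0.21 at a cut of 4 of 17, 0.105-0.117 at 5, and below 0.10 at 6 or more. These ranges assume a futility cut between none and 2. They do not cover repeated looks, which Section 16.1 leaves open.

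Separately, at the stated accrual, 4-5 of the 17 stage-1 patients would lack a week-12 result on 30 June 2014, the day before stage 2 is due to open. The fall in power from 0.79 to 0.74-0.76 (cut 1), or from 0.75 to 0.60-0.64 (cut 2), is a worst case only. It rests on assumed futility cuts, on counting unread patients as not controlled, and on estimated dates.

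**What to change.** - State in Sections 10.1 and 11 that the stage-1 efficacy look is for futility only, with safety stops kept separate. Delete the permission to stop for early positive outcomes in Sections 11 and 16.1. Alternatively, allow an early positive only once 9 disease controls have been observed, which costs no alpha.
- State that the stage-1 decision is taken only when every stage-1 patient has a week-12 assessment or an earlier failure, and that enrolment pauses until then.
- Redate Table 4 to allow 12 weeks after the last stage-1 entry, and check the stage-2 rows in the same way.

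The cost is a few sentences, new dates and an accrual pause of up to about 12 weeks. The pause is shorter if the stage-1 cut has already been exceeded. No extra patients are needed.

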13.1 Clinical Records (CRF)

A CRF is required and must be completed for each included patient and sent to the principal investigator within 90 days of the patient's discontinuation .

It is the responsibility of the investigator to ensure completion, review and approval of all CRFs. The CRF must be signed by the investigator or an authorized team member (co-investigator). These signatures serve to certify that the information contained in the CRF is true. At all times, the investigator has ultimate personal responsibility for the accuracy and authenticity of all clinical and laboratory data recorded with the CRF. Patient source documents (medical records) are the patient's medical records kept at the study institution.

14. Adverse Event

14.1 Definitions

An Adverse Event (AE) is defined as any unfavorable medical occurrence or experience, in a patient or patient under clinical investigation, that occurs after administration of study medication, regardless of dose or causal relationship. This may include any unfavorable and involuntary signs (such as rash or liver enlargement), or symptoms (such as nausea or chest pain), an abnormal laboratory finding (including blood tests, X-rays or CT scans) or a disease temporarily associated with use. of protocol treatment.

An Adverse Drug Reaction (ADR) is defined as any response to the medicinal product, which is harmful and / or unexpected, related to any dose.

Response to the medicinal product (used in the definition above) means that a causal relationship between the medicinal product and the adverse event is at least a reasonable possibility, ie the relationship cannot be ruled out.

An Unexpected Adverse Drug Reaction is any adverse reaction for which the nature or severity is not consistent with the information applicable to the product (eg, Investigator Brochure).

A Serious Adverse Event (EAS) is defined as any unwanted experience that occurs with a patient, whether or not considered related to protocol treatment. A Serious Adverse Event (EAS) that is considered related to protocol treatment is defined as a Serious Adverse Drug Reaction (RASM).

Adverse events and adverse drug reactions that are considered serious are those that result in:

• death;

• Risk of death (ie the patient had an immediate risk of death at the time the reaction was observed);

• Hospitalization for more than 24 hours or prolongation of hospitalization;

• Persistent or significant disability / disability;

• Congenital anomaly / birth defect;

• Any other clinically important condition (ie, major adverse reactions that are not life threatening or result in death or hospitalization but may endanger the patient or may require intervention to prevent one of the other consequences listed above).

The progression of malignancy under the study should not be reported as an adverse event as well as death due to disease progression.

14.2 Reporting Procedure

All observed or spontaneous adverse events, regardless of the suspected causal relationship with the investigational product, will be reported as described below.

For all adverse events, the investigator should seek and obtain appropriate information both to determine the outcome of the adverse event and to assess whether he meets the criteria for classification as a serious adverse event requiring immediate notification to the Research Ethics Committee. For all adverse events, sufficient information should be obtained by the investigator to determine the causality of the study drug. Event tracking is required until the event, or its consequences, is resolved or stabilizes at an acceptable level.

Adverse events (serious or non-serious) should be recorded in CRF from the moment the patient has received at least one dose of study treatment until the patient's last visit. Serious adverse events developed within 28 days of the last administration of the investigational product should be reported immediately to the Research Ethics Committee.

In accordance with Brazilian regulatory laws, the investigator must inform the local Research Ethics Committee about additional and study-specific problems every 6 months.

15. Quality Assurance

15.1 Data Compliance Control

During the conduct of the study, periodic monitoring visits will be conducted to ensure that the GCP (Good Clinical Practice) protocol and guidelines are followed. Monitors may review source documents and imaging studies to confirm that data recorded on the CRF (Clinical Record) is accurate. The investigator and the institution will allow the source documents to be monitored and appropriate regulatory authorities to have direct access to them in order to carry out verifications. The study institution may be subject to review by the Ethics Committee.

16. Ethical Considerations

This protocol and its consent form have already been approved by the research ethics committee of the proposing institution, Barretos Cancer Hospital. The free and informed consent form was prepared in compliance with ICH GCP guidelines, local regulatory regulations and legal requirements. It is the responsibility of the investigator to obtain future approval of protocol amendments and other documents relevant to the CEP.

The study will be conducted in accordance with the International Harmonization Conference (ICH GCP) Protocol, Good Clinical Practice guidelines, and applicable local regulatory laws and requirements (RDC 39-2008 ANVISA; RDC 196-1996; RDC 466-2012) .

The investigator should ensure that each study patient, or legal representative, is fully informed about the nature and objectives of the study and possible risks associated with participation. The investigator will obtain written consent from each patient before any specific study activity is performed. The investigator will retain a copy of each consent form signed by the patient.

Considering that human biological material is expected to be stored in our Hospital (biobank), in addition to meeting the requirements of Resolution CNS No. 466/12 and complementary, we clarify that:

There will be consent of the research subject, authorizing the collection, deposit, storage and use of human biological material (present in the IC);

This material will be under the supervision of the HCB Biological Material Committee, following all the precepts already in force of this body;

We declare that any future research to be conducted with the stored material will be submitted for approval by the institutional Research Ethics Committee and, where appropriate, the National Research Ethics Commission.

16.1 Patient Protection

The responsible investigator will ensure that this study is conducted in accordance with the Declaration of Helsinki (amendments from Tokyo, Venice, Hong Kong, Somerset West and Edinburgh) or with the laws and regulations of the country providing the highest patient protection.

The protocol has been written and the study will be conducted in accordance with the Tripartite Guidelines of the International Conference on Harmonization for Good Clinical Practice (http://www.ifpma.org/pdfifpma/e6.pdf).

The protocol has already been approved by the HCB Research Ethics Committee, which considered it unnecessary to submit for evaluation by the National Research Ethics Committee (CONEP). There will be continuous monitoring of safety and efficacy results by the Research Ethics Committee (CEP-HCB), as routine, in order to ensure the safety of the research subjects. If necessary, the study may be discontinued early either due to futility, lack of security or early achievement of its positive outcomes.

